##### Social network and informal care

Participants are asked if they receive informal care, how many hours a week, what type of care (housekeeping and/or personal care) and from which persons (partners, children, other family members or neighbours/volunteers).

##### Health-related quality of life

This will be measured by the EuroQoL-5D (EQ-5D). The EQ-5D is a broadly used and validated instrument for measuring generic HRQOL.^37^

#### Physical functioning

##### Risk of functional decline

Patients are assessed for risk of functional decline using the Identification of Seniors at Risk-Hospitalised Patients tool; scores of two and up indicate an increased risk for functional decline.^45^

##### Functioning level

The 15-item modified Katz-ADL score is used to measure ADL functioning. This includes statements about independence in performing basic ADL and in instrumental ADL (IADL).^46 47^ We measure the Katz-ADL both currently (at admission), as well as 2 weeks before admission, reflecting pre-morbid level of functioning. The Katz-ADL is also measured during follow-up.

##### (Im)mobility

Mobility is assessed by reviewing three questions that are in the admission assessment regarding: (1) the use of a walking aid, (2) being able to walk outside of the house for 5 min (2 weeks before and currently) and (3) the performance and frequency of physical activity.^48^

##### Handgrip strength

Measure muscle weakness is measured by physiotherapists in all admitted patients using the maximum handgrip strength (Jamar).^49^

##### Gait speed

Gait speed is measured as part of the Short Physical Performance Battery, which is part of the physiotherapists’ admission assessment.^50^

##### Falls

Fall history is assessed by asking about the number of falls in the past 6 months.^42^ During the discharge assessment, the occurrence of falls in the AGCH and the consequences of falls (indication for prolonged stay, diagnostics or injury) are recorded.

##### Fear of falling

*The* Numeric Rating Scale (NRS, score 0–10) is used to assess the fear of falling; 0 indicates no fear of falling, and 10 indicates the greatest fear of falling possible.^35^

##### Pain

The standard clinical measure for pain is the NRS, ranging from 0 to 10, in which a score of 0 represents no pain and 10 represents the worst possible pain.^51^

##### Fatigue

An NRS from 0 to 10 is used, with 0 indicating no fatigue and 10 indicating the greatest fatigue ever felt by the participant.^52^

##### Sleep

Participants are asked if they have had difficulties with sleeping in the past month and whether participants have used sleep medication.

##### Nutrition

We will use the Short Nutritional Assessment Questionnaire (SNAQ) to identify patients with malnourishment. The SNAQ consists of three questions concerning weight loss, appetite and drink/tube nutrition, resulting in a score ranging from 0 to 5. Scores of 0 and 1 are defined as ‘no malnutrition’, 2 as ‘moderate malnutrition’ and 3 or more as ‘severe malnutrition’.^53^

#### Healthcare utilisation and satisfaction with care

##### Medical care during admission and the process of discharge

The following items are collected from patients’ electronic health records: the diagnostics performed in the AGCH, revisits to the hospital, admissions to the hospital, length of stay at the AGCH, discharge destination and time needed to send medical handovers to the general practitioner.

##### Hospital readmission

This outcome will be assessed during follow-up. Follow-up will consist of three telephone interviews at 1, 3 and 6 months after discharge. Readmission will be both assessed during the follow-up interviews and by checking care data from an aggregated database of expense claims from various healthcare insurers. Data that will be collected are as follows: number of readmissions, total days of readmission, reasons for readmission and whether the readmission was planned or unplanned.

##### ED visits

ED visits will be assessed during follow-up and checked in the insurance data. We will record the number of separate ED visits.

##### Outpatient hospital visits

We will ask patients if there have been any outpatient visits in the past month(s), and if so, how many.

##### Consultations by general practitioners

We will ask patients if, and how many times, they have consulted with their general practitioner (both during the day and during out-of-office hours).

##### Consultations by physiotherapists or dieticians

We will ask patients if, and how many times, they have consulted with a physiotherapist or dietician in the past month(s).

##### Home care

This includes questions on the frequency of home care, including housekeeping, personal care and nursing care. We will also include hours of informal care provided by family members or friends.

##### Temporary admission to a nursing home

This includes days of (temporary) admission to a skilled nursing facility or rehabilitation facility.

##### Permanent institutionalisation

This concerns long-term admission to a skilled nursing facility and the date of admission to this facility.

##### Patient satisfaction with care

Patients or informal caregivers are asked to fill out an eight-question questionnaire regarding their satisfaction with the care that they received. Questions are answered on a five-point Likert scale.^54^

### Sample size calculation

In the Hospital-ADL study, 34% of participants experienced a readmission at 90 days.^35^ Assuming that 26% of patients admitted to the AGCH will experience a 90-day readmission, data from 515 patients at the AGCH will yield 80% power to detect an absolute difference of 8% in the readmission rate (which is a 25% reduction in the relative risk) using a two-sided test with an alpha of 0.05.^55^ As we expect 10% loss to follow-up, we aim to include a total of 567 (=515*1.10) patients from the AGCH.

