### Historical control groups

We selected two completed cohort studies that were conducted by our research group as historical control groups. We expect that the patients from these cohorts have similar admission diagnoses as those who can be admitted to the AGCH, namely, diagnoses that are ambulatory care sensitive conditions such as infections and exacerbations of chronic obstructive pulmonary disease (COPD) or heart failure.^32^ Patients in these two cohorts were admitted to internal medicine, cardiology, pulmonology and geriatrics departments. These departments admit patients with diagnoses similar to those that can be admitted to the AGCH. In addition, we have selected these cohorts as control groups as the patients come from the same area as the studied population admitted to the AGCH, that is, the greater Amsterdam area. The first control group from the Transitional Care Bridge Study consists of 674 patients who were recruited between September 2010 and March 2014.^33^ Participants were patients of 65 years and older hospitalised for at least 48 hours. Proxy consent was provided for participants suffering from severe cognitive impairment (MMSE ≤15). They participated in a negative randomised controlled trial that assessed the effectiveness of a nurse-led transitional care programme in preventing functional decline.^33^ The second control group from Hospital-Associated Disability and impact on daily Life study (Hospital-ADL study) consists of 401 patients who were recruited between October 2015 and June 2017.^10^ These participants were enrolled in a prospective cohort studying the trajectory of functional decline in older hospitalised adults. Participants were aged 70 years and older and were hospitalised for at least 48 hours. Patients suffering from severe cognitive impairment (MMSE ≤15) and delirium were excluded from participation. For the detailed methodology and inclusion criteria of the two control cohorts, please refer to the study protocols and papers of these studies.^10 33–35^

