### Outcomes

The primary outcome measure is the 3-month unplanned readmission rate to the AGCH or hospital.

Secondary outcomes measured at 1, 3 and 6 months will include:

Activities of Daily Living (ADL)-functioning, as defined by the Katz-ADL scale.^36^Healthcare utilisation, including institutionalisation in a long-term care facility.Occurrence of delirium and/or falls.HRQOL.^37^All-cause mortality.Satisfaction of the patients and primary caregivers with the provided care.

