### Planned statistical analyses

The complete participant flow diagram will show a summary of admissions and study recruitment at the AGCH and will provide study discontinuation rates at 1, 3 and 6-months follow-up.^30^ We will describe the demographic, clinical and prognostic characteristics of the study participants at baseline. The number of participants with missing data will be collected and described alongside our variables to check for the pattern of missingness. Inversely weighted propensity scores will be used to control for any imbalances between the treatment groups.^56^ Propensity scores will be calculated using generalised booted methods. Balance and overlap of propensity score distribution will be assessed. Propensity score weights for the estimation of the average treatment effect will be created using all covariates where groups differed at baseline or that were associated with the 90-day readmission rate. As this is a repeated measures design, we will assume equal weighting for all measurements.^57^

All hypotheses will be tested using a two-tailed significance level of 0.05. All secondary outcomes will be adjusted for multiple testing using a Hochberg method.^58 59^ Descriptive analyses will be performed to examine the participants’ characteristics. Differences in changes over time in outcomes will be compared between groups using multilevel models. All models will include a main effect of treatment group, a linear term for time and an interaction between time and treatment group. Models will be checked with residual and appropriate goodness-of-fit statistics.

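### The 80% power for 515 AGCH patients is an unweighted 1:1 figure that matches neither the available controls nor the weighted analysis; actual power may be above or below 80%

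*Protocol article*

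**What the plan says.** All references are to the protocol article.

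- **Sample size calculation.** The control rate comes from one cohort: "In the Hospital-ADL study, 34% of participants experienced a readmission at 90 days". The AGCH rate is assumed: "Assuming that 26% of patients admitted to the AGCH will experience a 90-day readmission". The claim is that "data from 515 patients at the AGCH will yield 80% power to detect an absolute difference of 8% in the readmission rate", "using a two-sided test with an alpha of 0.05". The recruitment target follows from it: "As we expect 10% loss to follow-up, we aim to include a total of 567 (=515*1.10) patients from the AGCH". The paragraph gives no number of controls, no allocation ratio and no allowance for weighting.
- **Historical control groups.** There are two completed cohorts. The Transitional Care Bridge cohort has 674 patients. The Hospital-ADL cohort "consists of 401 patients who were recruited between October 2015 and June 2017". Together they have 674 + 401 = 1075. The article does not say whether they are pooled or compared with the AGCH separately.
- **Planned statistical analyses.** "Inversely weighted propensity scores will be used to control for any imbalances between the treatment groups". The weights target the average treatment effect, so both groups are weighted.
- **Abstract, Methods and analysis.** Here the adjustment method is propensity score matching.
- **Outcomes.** "The primary outcome measure is the 3-month unplanned readmission rate to the AGCH or hospital".

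**The concern.** The power statement is the only justification given for recruiting 567 AGCH patients, and it will be the yardstick for a non-significant primary result. It appears to describe 515 AGCH patients against 515 controls, compared directly. No control set in the article has 515 patients, and the detailed analysis is not a direct comparison.

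The error could run either way. If power is below 80%, a null result would be over-read as evidence against an 8-point reduction. If both cohorts are pooled and weighting costs little, the target is larger than 80% power requires. A reader cannot tell which from the article.

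A smaller mismatch sits alongside. The 34% is described simply as readmission, while the primary outcome counts unplanned readmissions only.

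**Working it through.** **Inputs.** From Sample size calculation: control rate p1 = 0.34, AGCH rate p2 = 0.26, difference 0.08, two-sided alpha 0.05 (z = 1.960), power 80% (z = 0.842), AGCH n = 515. From Historical control groups: 401, 674 and, by addition, 1075 controls. The design effect of weighting is not in the article, so it is assumed and varied from 1.0 to 2.0.

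**Step 1. Reproduce the plan's figure.** With equal groups and p̄ = 0.30,

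n per group = [1.960·√(2·0.30·0.70) + 0.842·√(0.34·0.66 + 0.26·0.74)]² / 0.08² = 513.9, rounded up to 514.

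The unpooled-variance version gives 512 and the arcsine version 514. Power at 515 versus 515 is 80.1%. So 515 is the per-group size of an unweighted 1:1 comparison.

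**Step 2. Put in the controls that exist, without weighting.** For nC controls and nA = 515,

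power = Φ{ [0.08 − 1.960·√(p̄(1−p̄)(1/nC + 1/nA))] / √(p1(1−p1)/nC + p2(1−p2)/nA) }, with p̄ the size-weighted mean of 0.34 and 0.26.

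For 401 controls, p̄ = 0.295, the null standard error is 0.03037 and the alternative standard error 0.03055. The argument is (0.08 − 1.960·0.03037)/0.03055 = 0.670, and Φ(0.670) = 74.9%.

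| Controls | nC | Power with 515 AGCH | AGCH patients needed for 80% |
|---|---|---|---|
| Hospital-ADL alone | 401 | 74.9% | 699 |
| Transitional Care Bridge alone | 674 | 84.7% | 420 |
| Both pooled | 1075 | 90.2% | 344 |

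None of the three gives 80%.

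**Step 3. Allow for weighting.** Weighting with unequal weights behaves approximately like dividing each group's size by a design effect (DE). Applying the same DE to both groups gives:

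| Assumed DE | 401 | 674 | 1075 |
|---|---|---|---|
| 1.0 | 74.9% | 84.7% | 90.2% |
| 1.2 | 67.1% | 77.6% | 84.3% |
| 1.5 | 57.5% | 68.1% | 75.4% |
| 2.0 | 46.1% | 55.6% | 62.7% |

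Power reaches 80% at a DE of about 1.34 for the pooled controls and about 1.13 for Transitional Care Bridge alone. For Hospital-ADL alone it is below 80% even at DE 1.0.

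**Step 4. Is a sizeable DE plausible?** The article gives some reason to expect imperfect overlap. Hospital-ADL excluded delirium and severe cognitive impairment. Delirium is one of the geriatric conditions that qualify a patient for AGCH admission (Setting), and 29.2% of AGCH consents were given by a proxy (Preliminary results). This makes a DE above 1 likely but does not fix its size.

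**The case against.** The strongest reply has four parts.

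1. **The study has more controls than the calculation needs.** Both cohorts are named as the control population. Pooled, they give 90.2% unweighted, and Transitional Care Bridge alone gives 84.7%. Using Hospital-ADL for the planning rate does not make it the comparator. This stands. A reader might infer from the 1:1 figure that the design lacks its stated power, but the article does not support that. It follows without further assumption only for Hospital-ADL alone, and nowhere is that declared the primary comparison.
2. **Any pooled figure below 80% rests on an assumed design effect.** This also stands. The article gives no overlap or weight distribution. The DE approach also ignores precision that may be gained by balancing covariates related to readmission, so it may understate power.
3. **The abstract's matching could rescue the 1:1 figure.** A pool of 1075 could in principle supply 515 matched controls, and the Discussion also speaks of matching. But the detailed analysis section specifies weighting for the average treatment effect, and the sample size paragraph does not mention matching. The conflict is a reason to settle the method; it does not validate the 80%.
4. **The 34% may already count only unplanned readmissions.** The cited source is not at hand, and the article elsewhere shortens its own primary outcome to a 90-day readmission rate. So a reader should not conclude that the planning rate is wrong, and no size can be put on this point. It only needs confirming.

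It can also be said that a condensed article may leave the control number and weighting allowance to a fuller document. That would excuse silence. Here the article publishes a specific power and a target derived from it, beside controls and an analysis to which they do not correspond.

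**Conclusion.** The arithmetic behind 515 is correct, but for a comparison that the detailed analysis does not plan. At the stated rates, unweighted power with 515 AGCH patients is 74.9%, 84.7% or 90.2%, depending on which controls are used, and weighting lowers each by an unknown amount. For the pooled controls the result is at or above 80% up to a DE of about 1.34 and below it beyond that.

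The supportable conclusion is therefore that the 80% is not tied to the planned comparison and that true power may lie on either side of it. The unweighted figures rest only on the article's own numbers and on all of the patients listed in each cohort contributing. The weighted figures rest in addition on an assumed, equal DE in both groups. Because the statement sets the 567 target and will frame the primary result, it should be corrected rather than left as a matter of wording.

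**What to change.** Restate the sample size paragraph for the comparison that will be made:

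- Name the control set for the primary analysis, pooled or separate, and give its actual number.
- Confirm whether the 34% counts unplanned readmissions only. If not, replace it with the unplanned 90-day rate in the chosen control set.
- Choose matching or weighting, and make the abstract, Discussion and analysis section agree, so that the calculation refers to one method.
- Replace the 80% by the power, or by the difference detectable with 80% power, at the effective sample size after adjustment. If weighting is kept, estimate this as (Σw)²/Σw² in each group, using the 212 AGCH baselines already collected and the historical data the research group holds.

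The cost is a short calculation and some rewording, with no extra patients. The drawback is that the stated power may turn out less favourable than 80%.

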### Planned statistical analyses

The complete participant flow diagram will show a summary of admissions and study recruitment at the AGCH and will provide study discontinuation rates at 1, 3 and 6-months follow-up.^30^ We will describe the demographic, clinical and prognostic characteristics of the study participants at baseline. The number of participants with missing data will be collected and described alongside our variables to check for the pattern of missingness. Inversely weighted propensity scores will be used to control for any imbalances between the treatment groups.^56^ Propensity scores will be calculated using generalised booted methods. Balance and overlap of propensity score distribution will be assessed. Propensity score weights for the estimation of the average treatment effect will be created using all covariates where groups differed at baseline or that were associated with the 90-day readmission rate. As this is a repeated measures design, we will assume equal weighting for all measurements.^57^

All hypotheses will be tested using a two-tailed significance level of 0.05. All secondary outcomes will be adjusted for multiple testing using a Hochberg method.^58 59^ Descriptive analyses will be performed to examine the participants’ characteristics. Differences in changes over time in outcomes will be compared between groups using multilevel models. All models will include a main effect of treatment group, a linear term for time and an interaction between time and treatment group. Models will be checked with residual and appropriate goodness-of-fit statistics.

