### Economic evaluation

A healthcare and societal perspective is planned for the economic evaluation. The evaluation from the healthcare perspective will only include direct medical costs accrued in the 6 months after the admission to the AGCH. Direct medical costs will only include costs that are funded through the Dutch healthcare system. The evaluation from a societal perspective will include an estimation of the costs of informal care. Costs will be based on the reference prices found in the Dutch Manual for Costing studies and will be set for the final year of data collection (2020 or 2021). According to this guideline, costs will be discounted at 4% and quality adjusted life years (QALY) will be discounted at 1.5%.^60^ Propensity scores will also be used in the economic evaluation. Missing data will be imputed using multiple imputation chained equations, if necessary, for the cost and effect data. We plan to use generalised linear regression models with a gamma distribution and an identity link to account for the right skew of the cost data. A generalised linear regression model will be used to estimate the incremental effect in QALY adjusted for baseline utility estimates with a Gaussian distribution and identify link.^61^ Incremental cost-effectiveness ratios will be calculated using the pooled cost and effect estimates. Bootstrapped cost-effect pairs will be plotted on a cost-effectiveness plane and used to estimate cost-effectiveness acceptability curves.^62^

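### The propensity-weight covariates are chosen by observed baseline difference or association with readmission, not from a prognostic list fixed in advance

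*Protocol article*

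**What the plan says.** All of the adjustment text is in the protocol article, under Planned statistical analyses, with one further sentence under Economic evaluation.

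- **Method:** "Inversely weighted propensity scores will be used to control for any imbalances between the treatment groups".
- **Propensity model:** "Propensity scores will be calculated using generalised booted methods" (presumably boosted).
- **Target and covariates:** "Propensity score weights for the estimation of the average treatment effect" are to be "created using all covariates where groups differed at baseline or that were associated with the 90-day readmission rate".
- **Diagnostics:** "Balance and overlap of propensity score distribution will be assessed".
- **Wider use:** "Propensity scores will also be used in the economic evaluation".

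The article names no covariates for the weights. It gives no criterion for when groups count as having differed, and does not say in which data, or on what knowledge, association with readmission is judged. This is a stated selection rule, so it is not a detail merely left to an analysis plan.

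**The concern.** In a comparison with historical controls, the choice of covariates largely decides how far the result can be trusted. The rule has two weaknesses.

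**It admits variables for the wrong reason.** A confounder must be related both to group and to outcome, but the first limb asks only about group. Group differences are built into this design. The controls were recruited in 2010–2014 and 2015–2017 and had been in hospital for at least 48 hours, and one cohort excluded severe cognitive impairment and delirium (Historical control groups). AGCH patients were recruited from 2019 in a different setting, with proxy consent possible (Study design; Participants). Weighting on a variable that separates the groups but does not predict outcome removes no confounding. It makes the weights more variable, thins the overlap, and can enlarge whatever bias unmeasured confounders leave. The Discussion itself acknowledges that hospital work processes may have changed over the years.

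**It settles the set from the data.** Whether groups differed is known only once they are compared. The second limb names the primary outcome, and its natural reading is association seen in the study data. An analyst could then arrive at the adjustment set with the result in view.

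**Working it through.** **1. The plan's own figure.** Inputs from Sample size calculation: control readmission 34% ("In the Hospital-ADL study, 34% of participants experienced a readmission at 90 days"), AGCH 26% ("Assuming that 26% of patients admitted to the AGCH will experience a 90-day readmission"), two-sided alpha 0.05, power 80%. The two-proportion formula with pooled variance and 1:1 groups gives 514 per group. The stated 515 gives 80.1% power, so it reproduces. Against all 674 + 401 = 1,075 controls (Historical control groups), 515 AGCH patients give 90% power before weighting. That is the reference below, and it assumes both cohorts are used in full.

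**2. Cost of one non-prognostic binary covariate.** The prevalences are assumed; the documents give none. Within each level of the covariate:

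- propensity e = AGCH count / total count; weight 1/e for AGCH and 1/(1 − e) for controls
- effective n per group = (Σw)² / Σw²
- variance inflation = (1/ESS_A + 1/ESS_C) / (1/515 + 1/1,075)

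Worked case, 20% in AGCH v 80% in controls:

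- Counts with and without the covariate: AGCH 103 and 412; controls 860 and 215; totals 963 and 627.
- AGCH weights: 963/103 = 9.35 and 627/412 = 1.52. Control weights: 963/860 = 1.12 and 627/215 = 2.92. Weights sum to 1,590 in each group.
- ESS_A = 1,590² / (963²/103 + 627²/412) = 2,528,100 / 9,958 ≈ 254.
- ESS_C = 1,590² / (963²/860 + 627²/215) = 2,528,100 / 2,907 ≈ 870.
- Inflation = (1/254 + 1/870) / (1/515 + 1/1,075) = 0.00509 / 0.00287 ≈ 1.77.

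| Prevalence | Standardised difference | AGCH effective n | Variance inflation | Power, 34% v 26% |
|---|---|---|---|---|
| no such covariate | 0 | 515 | 1.00 | 90% |
| 45% v 55% | 0.20 | 506 | 1.01 | 90% |
| 40% v 60% | 0.41 | 479 | 1.06 | 89% |
| 30% v 70% | 0.87 | 382 | 1.26 | 82% |
| 20% v 80% | 1.5 | 254 | 1.77 | 68% |
| 10% v 90% | 2.7 | 121 | 3.44 | 40% |

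**3. Simulation check.** Settings: 1,590 patients, logistic propensity model (not the planned boosted one), no treatment effect, 800 runs per setting, one measured confounder always in the weights, and a continuous non-prognostic marker left out or put in. Standard error of the risk difference, without → with the marker, by the marker's log-odds for group per SD:

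- 0.3: 0.026 → 0.026
- 0.5: 0.025 → 0.027
- 1.0: 0.024 → 0.030
- 1.5: 0.024 → 0.038
- 2.0: 0.024 → 0.051

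With no unmeasured confounding, the estimate was essentially unbiased with or without the marker. With an unmeasured confounder (log-odds 0.4 for both group and outcome), adding the marker raised the residual bias from 0.029 to 0.036 at strength 1.0, and from 0.020 to 0.033 at 2.0.

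**4. How far the first limb could turn on chance.** If groups were taken to differ when p < 0.05 (an assumption; no test is stated), a true standardised difference of 0.10 would be flagged in 32% of studies with 515 v 401 patients and in 46% with 515 v 1,075.

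**The case against.** The case against is substantial, and several stronger readings fail.

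- **That the weights are tuned only to readmission.** A reader might infer this because the outcome limb names only readmission, while the scores also serve the economic evaluation and no other weights are described for the secondary outcomes. The rule does not support it. Its first limb refers to no outcome, so a measured confounder of function, quality of life, mortality or cost enters where its group difference is detected. The QALY model also adjusts for baseline utility.
- **That the set cannot be fixed until outcomes are seen.** Both control cohorts are complete, and the sample size already uses a readmission rate from one of them. Association could be judged in controls alone or from prior knowledge. Choosing after sight of AGCH outcomes is allowed by the wording, not required by it.
- **That a difference is defined by a significance test, and so by sample size.** No test is stated. Step 4 of the working is conditional on that assumption.
- **That a large loss of power should be expected.** The 68% and 40% figures need a covariate that nearly separates the groups yet is unrelated to outcome. The collected variables (comorbidity, drugs, cognition, function, nutrition, falls) are mostly plausible prognostic factors, and no non-prognostic marker can be named among them. At moderate imbalance the cost is 1% to 6% of variance.
- **That a non-prognostic covariate biases the estimate.** Alone it does not; amplification needs unmeasured confounding as well.

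Boosting and the balance and overlap checks may soften the harm. The checks can reveal poor overlap, but they do not change which variables are allowed in. What stands is that the first limb is data-driven on any reading, and that nothing in the article fixes the set in advance.

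**Conclusion.** The point holds as a fault in the stated rule. Entry on a baseline difference alone can bring non-prognostic group markers into the weights, and the adjustment set is left to the data, on the natural reading partly to the primary outcome. The main harm is lost precision and overlap, with possible amplification of unmeasured confounding. Its size ranges from negligible (inflation 1.01 to 1.06) to large (1.77 to 3.4), depending on an imbalance that the documents do not give. The figures rest on assumed prevalences, a single covariate, use of all 1,075 controls, and simple weights in place of the boosted model. The documents do not show that any such marker will enter, or that the analysts intend to choose covariates after seeing AGCH outcomes. The change is worth making because it is cheap and closes off both possibilities.

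**What to change.** Replace the selection rule with a named list of baseline covariates, chosen on prior prognostic knowledge for readmission and for the key secondary and economic outcomes. Take them from variables already collected and available in comparable form in the cohorts. Candidates are age, sex, living arrangement, education, Katz-ADL for two weeks before admission, cognition, Charlson index, number of drugs, hospitalisation in the past 6 months and admission diagnosis. Comparability has to be confirmed against the supplementary measurement table, which is not shown here.

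- Fix and date the list before AGCH outcomes are examined.
- Do not add a variable only because the groups differ on it.
- Judge balance by weighted standardised differences (for example, below 0.1).
- Put listed variables that stay imbalanced into the outcome model as well.
- Check overlap on cognition specifically. One control cohort excluded MMSE ≤15 and delirium, and the MMSE is not done in patients who are delirious at inclusion. Prespecification does not cure that.

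The cost is one paragraph of text. At the last reported count (Preliminary results), 212 of the planned 567 patients had been included, so at that stage the list could still be set in good time. The small downside is that an omitted variable that differs and proves prognostic would be handled only in a sensitivity analysis.
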